### Aims and hypotheses

1.1

This study aims to compare suicide risk estimates across different populations and conditions. Specifically, the objectives are: (i) to compare suicide risk evaluations across the different study groups; (ii) to examine the temporal stability of suicide risk estimates when participants evaluate different but comparable clinical scenarios over time; and (iii) to assess whether the use of a structured instrument (C-SSRS) is associated with greater convergence in risk classification compared to unstructured judgment based on personal or clinical impressions. In addition to group-based comparisons, the study will examine whether differences are better explained by dimensional indicators of clinical experience rather than by professional labels alone.

Additionally, based on the expected results, the following hypotheses were formulated:

*HP 1*: Greater clinical experience and prior exposure to suicide-specific training will be associated with higher agreement and more consistent suicide risk estimates, regardless of professional category (Aim 1).

*HP 2*: Differences in risk estimation are expected to reflect variability in clinical exposure to acute suicidal presentations rather than disciplinary background per se (Aim 1).

*HP 3*: All study groups will show lower agreement for intermediate risk categories compared to low and high-risk categories (Aim 1 and 2).

*HP 4*: Greater within-subject variability is expected among individuals with limited or no clinical exposure to suicidal behavior compared to those with greater prior clinical exposure. This expectation is based on the idea that personal experiences, momentary emotional states, and situational cues may exert a stronger influence on individuals who are not familiar with clinical decision-making, whereas healthcare professionals are trained to rely primarily on clinical information and data (Aim 2).

*HP 5*: Participants assigned to the experimental condition (brief training on suicide risk assessment and use of the C-SSRS) will exhibit greater between-subjects and within-subject agreement in suicide risk estimates across all study groups (Aim 3).

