#### Baseline assessment

2.3.1

The study procedures and enrollment process are shown in **Figure 2**. During the baseline assessment, participants will be asked to answer sociodemographic questions as well as to indicate their professional and academic background, in order to assign them to a specific study group. Then, participants of each group (i–x) will be randomly assigned to one of the two conditions (C-SSRS *vs.* No-C-SSRS).

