**Figure 2 f2:**
[figure not shown]
Conceptual framework of the CARE study showing the baseline and follow-up assessments.

The questionnaire will be designed so that each participant will be randomly assigned to 6 different vignettes to be evaluated, 2 for each risk category (low, moderate, and high). Specifically, participants assigned to the C-SSRS condition will complete a brief training module on basic suicidology notions embedded within the online questionnaire before evaluating the vignettes. The module is delivered as a single self-administered page and requires approximately 5 minutes to be completed. It is divided into two sections: first, it will provide concise definitions of suicide-related constructs, including thoughts of death, suicidal ideation, suicidal planning, non-suicidal self-injury, suicide attempt, and suicide death, in order to reduce interpretative variability across respondents; second, it will present step-by-step instructions on how to use the C-SSRS (14), explaining the logic of the six screening questions, when conditional questions are administered, and how responses map onto the three risk categories defined by the scale (low, moderate, high). Ultimately, participants will be provided with access to the official Italian version of the C-SSRS and informed that a mobile application version can be used if preferred. No feedback, supervision, or competency assessment will be provided, thereby reflecting the type of brief orientation often available in real-world implementation settings. The remaining participants will be asked to provide a subjective estimation of perceived suicide risk based on their impressions, knowledge, personal judgment, or clinical experience (for clinicians). Notably, for participants without a clinical background, the task is framed as an estimation of perceived suicide risk rather than a diagnostic or clinical evaluation. They will not be required to make clinical decisions but are instead asked to describe how they would interpret and respond to the situation described in the vignette. Participants assigned to the C-SSRS condition will be instructed, for each vignette, to provide a categorical rating of suicide risk as defined by the scale (low, moderate, high); whereas those assigned to the No-C-SSRS condition will be asked, for each vignette, to provide an ordinal risk estimate on a scale from 1 (very low risk) to 9 (imminent risk). Notably, the use of different response formats across conditions reflects the distinct decision-making frameworks under investigation. The C-SSRS operationalizes suicide risk through predefined categorical classifications and does not provide a continuous scoring system, while a 1–9 ordinal scoring metric will be adopted for the No-C-SSRS condition to better capture the natural variability of subjective risk appraisal without imposing a fixed, limited categorization. This approach allows the study to compare two ecologically valid assessment paradigms, structured categorical evaluation versus dimensional judgment, rather than two versions of the same measurement model.

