
In addition, licensed mental health professionals (psychiatrists and licensed psychologists) will be asked to provide clinical recommendations and to describe risk mitigation strategies they would use for each vignette scenario, whereas all other participants will be asked to describe how they would respond or behave in the described situations. At the end of the vignette assessment, all participants will be asked to report whether they have ever attended specialized training focused on suicide risk assessment or whether they have previously used the C-SSRS.

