#### Study variables

2.4.1

The online questionnaire will collect sociodemographic data (e.g., age, sex, educational level) and professional and academic background information. Specifically, all participants will be asked to indicate whether they have a professional or academic background in the medical or psychological fields (e.g., professional role, current year of psychiatry residency, years since completion of psychiatry specialization, current year of psychotherapy training, years since completion of psychotherapy specialization, year of study in a psychology degree program, year of study in a medical degree program), their specific field of practice (e.g., medical specialty area, psychotherapy orientation, nursing field, no prior experience in the medical or psychological field), and their clinical experience (e.g., years of practice, primary psychotherapy orientation, supervision, years of personal therapy). Responses to these preliminary questions will be used to automatically assign each participant to the appropriate study group. After the completion of the suicide risk assessment based on six vignettes describing hypothetical scenarios, all participants will be asked to indicate whether they have ever completed a suicide risk assessment training or previously used the C-SSRS scale.

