To quantify inter-rater agreement across raters for each vignette, Krippendorff’s alpha will be used as the primary agreement index, as it is appropriate for multi-rater settings with potentially unbalanced data. Weighted kappa coefficients will be computed only in supplementary pairwise comparisons to facilitate interpretability relative to commonly reported agreement metrics. Within-person analyses will evaluate the stability of participants’ overall level and pattern of risk estimates across time using different vignette sets drawn from the same risk-calibrated pool. These analyses do not represent test–retest reliability of identical stimuli but rather the temporal consistency of risk perception. Because different vignettes of the same risk category will be administered at baseline and follow-up, within-person analyses will be conducted on participant-level summary indices (e.g., central tendency of ratings and distribution of risk categories across vignettes at each time point) rather than on vignette-level paired comparisons. For the No-C-SSRS condition, paired non-parametric tests, such as the Wilcoxon signed-rank test, and correlation analyses will be used. For the C-SSRS condition, indices of temporal consistency will be computed to evaluate the stability of participants’ overall tendency to classify scenarios into risk categories across time, rather than agreement on identical stimuli.

The mixed-effects framework described above will also be used to examine interaction effects. Pre-specified interaction terms will examine whether differences in risk estimation vary as a function of demographic and professional variables (e.g., age, gender, years of clinical experience, prior suicide-specific training) across study group and experimental condition. In addition, to control for inflation of Type I error due to multiple comparisons, p-values from secondary analyses will be adjusted using the false discovery rate approach.

Missing data will be handled under a missing-at-random assumption using maximum likelihood estimation within mixed-effects models, which allows inclusion of all available observations without listwise deletion. Attrition between baseline and follow-up will be examined descriptively, and sensitivity analyses will compare participants who completed follow-up with those who did not. Predictors of attrition will be explored to assess potential systematic differences between completers and non-completers.

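### Prior suicide-specific training, an HP1 predictor and planned interaction variable, is asked only after one arm has completed the study's own training, so answers can differ by arm

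*Protocol article*

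**What the plan says.** Section 2.3.1 of the protocol article sets the order of events. Sociodemographic and professional questions come first. Participants in each of the ten groups then "will be randomly assigned to one of the two conditions". Next, the C-SSRS arm alone works through a short online suicidology module, and then rates six vignettes with the scale. The No-C-SSRS arm receives no module and rates from its own judgement. Only then comes the history question: "At the end of the vignette assessment, all participants will be asked to report whether they have ever attended specialized training". The item covers training in assessing suicide risk and earlier use of the C-SSRS.

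Section 2.4.1 repeats this placement after the six vignettes: "all participants will be asked to indicate whether they have ever completed a suicide risk assessment training or previously used the C-SSRS scale".

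The training variable has two planned uses. HP1 in Section 1.1 states: "Greater clinical experience and prior exposure to suicide-specific training will be associated with higher agreement" and more consistent estimates. Section 2.5.2 lists "years of clinical experience, prior suicide-specific training" among the variables whose interactions will be examined across study group and experimental condition.

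HP5 in Section 1.1 describes the experimental arm as follows: "Participants assigned to the experimental condition (brief training on suicide risk assessment and use of the C-SSRS".

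**The concern.** HP1 and the planned interaction both treat prior training as something the participant brought to the study. As scheduled, it is recorded after randomisation and after an exposure given to one arm only. The description in Section 2.4.1 (ever having completed a suicide risk assessment training) is close to the words HP5 uses for the study's own module. Nothing in the article says that participants are told to leave the module out, and no reason is given for the late placement. The other background variables that Section 2.4.1 describes are collected as preliminary questions, before assignment.

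At stake are the HP1 association wherever C-SSRS participants contribute to it, and the training-by-condition interaction. The interaction is the more exposed of the two, because the error can arise in one arm and not in the other. The planned data would not show which individual yes answers came from the study.

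**Working it through.** The plan gives no figure on this point. Its minimum of 400 participants (Section 2.5.1: ten groups, f = 0.20, alpha 0.05, power 0.80) reproduces: with df 9 and 390 and noncentrality 0.20² × 400 = 16, power is 0.8003. It does not depend on question order.

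**Order of measurement.** Background questions → randomisation → module and C-SSRS use (C-SSRS arm only) → vignettes → history question. Sections 2.3.1 and 2.4.1 agree, so this is a stated choice and not a gap left by a condensed article.

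**Illustration of size.** None of these inputs is in the documents; all are assumptions:
- p = true share with prior training, equal in both arms by randomisation;
- q = share of untrained C-SSRS participants who answer yes because of the module;
- no false yes in the No-C-SSRS arm, and no false no in either arm;
- the same true training effect d, a difference in mean participant-level score, in both arms;
- among the untrained, a false yes is unrelated to how they rate.

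The reported yes rate in the C-SSRS arm is p + (1 − p)q, against p in the other arm. Everyone answering no is untrained. Those answering yes are truly trained in the proportion p / [p + (1 − p)q]. The observed training effect in the C-SSRS arm is therefore d × p / [p + (1 − p)q]. The spurious interaction is that value minus d.

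Example, p = 0.20 and q = 0.10: yes rate = 0.20 + 0.80 × 0.10 = 0.28; observed effect = 0.20 / 0.28 = 0.71d; spurious interaction = −0.29d.

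Each cell gives the C-SSRS-arm yes rate, then the observed effect as a multiple of d:

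| p | q = 0.05 | q = 0.10 | q = 0.20 |
|---|---|---|---|
| 0.10 | 14.5%; 0.69 | 19%; 0.53 | 28%; 0.36 |
| 0.20 | 24%; 0.83 | 28%; 0.71 | 36%; 0.56 |
| 0.30 | 33.5%; 0.90 | 37%; 0.81 | 44%; 0.68 |
| 0.50 | 52.5%; 0.95 | 55%; 0.91 | 60%; 0.83 |

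The observed effect runs from 0.36d to 0.95d and the spurious interaction from −0.64d to −0.05d. At q = 0 both biases vanish. At q = 1 everyone in the C-SSRS arm answers yes and the variable carries no information there.

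**Would a comparison of yes rates by arm reveal it?** Only in part. Take 250 per arm, half of the planned 500. For 28% against 20%, the standard error of the difference is √(0.28 × 0.72/250 + 0.20 × 0.80/250) = 0.038, so a gap of 0.08 is about 2.1 standard errors. For 24% against 20% it is √(0.24 × 0.76/250 + 0.20 × 0.80/250) = 0.037, so a gap of 0.04 is about 1.1. A small misreport rate could pass unnoticed.

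**The case against.** The strongest reply is that the documents show the order but not the misreporting. Sections 2.3.1 and 2.4.1 describe the items without reproducing them, and the Italian questionnaire may already exclude the study. Section 2.3.1 speaks of attending specialised training, which one self-administered page of about five minutes hardly resembles. Section 2.1 says the module is not meant as skills-based training. This stands as a limit: the variable can be affected by arm, and a reader who infers that it is affected goes beyond the text. It does not remove the point, because the description in Section 2.4.1 fits the module and nothing shown tells participants otherwise.

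Other stronger readings are also unsupported:
- That prior C-SSRS use shares the problem in equal measure. Both sections say previously used, which gives some protection, and that variable is named neither in HP1 nor among the interaction examples in Section 2.5.2.
- That the randomised comparison is biased. It is not, unless prior training enters the model.
- That an HP1 association could be created from nothing. If false yes answers are unrelated to ratings, they only dilute a true effect, and a spurious interaction also needs a true effect. The No-C-SSRS arm still gives an HP1 estimate free of this error. If those who count the module are also those who absorbed it best, the direction is no longer fixed, but the documents do not speak to that.
- That most yes answers in the C-SSRS arm would be wrong. That occurs only in the corner of low prevalence and high misreporting (p = 0.10, q = 0.20: 0.18/0.28 = 64%). At p = 0.50 and q = 0.05 the share is 0.025/0.525 = 5%.
- That exposure to acute suicidal presentations is not collected. The lists in Section 2.4.1 are examples, so absence from them shows nothing.

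Late placement also has a possible merit. Naming the C-SSRS before randomisation could alert unsupervised No-C-SSRS participants to a tool which, according to the Introduction, has a public application giving an immediate risk estimate. That is a good reason to leave the C-SSRS item where it is. It does not apply to a general training question that need not name the scale.

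**Conclusion.** The point holds in a limited form. A variable used as a pre-existing characteristic, in a named hypothesis and in a pre-specified interaction with condition, is measured after an exposure that only one arm receives and that the question as described could include. If some untrained C-SSRS participants answer yes on that account, a true training effect shrinks in that arm and the training-by-condition interaction is biased. Over the assumed ranges (10–50% truly trained, 5–20% false yes), the effect observed in that arm is about 0.36 to 0.95 of the true one. The actual rate is unknown, and zero misreporting means zero bias. Confidence is high on the timing and the planned use of the variable, and low on the size. No stated figure in the plan changes. The change is worth making because it is cheap and because analysis cannot reliably recover the true answers afterwards.

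**What to change.** Ask the prior-training item with the sociodemographic and professional questions, before randomisation, worded 'before today'. Keep the prior C-SSRS item after the vignettes, word it to exclude use in this study, and compare its yes rates by arm. Amend Sections 2.3.1 and 2.4.1 to match.

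If recruitment has already started, add the exclusion wording to both items at once. Compare yes rates by arm for answers already collected, give the HP1 estimate from the No-C-SSRS arm alone as a sensitivity analysis, and report any training-by-condition interaction with this caveat.

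The cost is moving one survey item and rewording two. Asking about training early may prime participants slightly, but before randomisation that is balanced across arms in expectation. Sample size and the main analysis stay as they are.

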#### Follow-up assessment

2.3.2

Two weeks after completing the baseline questionnaire, each participant will receive an email reminder to complete the follow-up questionnaire. The follow-up assessment will require participants to evaluate 6 vignettes (2 per risk category), randomly selected from the same pool of 18 vignettes, to examine consistency between baseline and follow-up ratings. Notably, different vignettes are intentionally administered at follow-up to avoid recall effects and to evaluate the temporal stability of participants’ general risk estimation approach rather than agreement on identical cases. Participants assigned to the C-SSRS condition at baseline will again be asked to provide a categorical rating of suicide risk as defined by the C-SSRS (low, moderate, high), although no informational training will be provided at follow-up. Concurrently, participants in the No-C-SSRS condition will be asked, for each vignette, to provide an ordinal suicide risk rating from 1 (very low risk) to 9 (imminent risk), following the same procedure used at baseline. If participants do not complete the follow-up questionnaire within five days of receiving the first reminder, up to three additional reminders will be sent, each one three to five days apart.

### Variables and outcomes

2.4

#### Study variables

2.4.1

The online questionnaire will collect sociodemographic data (e.g., age, sex, educational level) and professional and academic background information. Specifically, all participants will be asked to indicate whether they have a professional or academic background in the medical or psychological fields (e.g., professional role, current year of psychiatry residency, years since completion of psychiatry specialization, current year of psychotherapy training, years since completion of psychotherapy specialization, year of study in a psychology degree program, year of study in a medical degree program), their specific field of practice (e.g., medical specialty area, psychotherapy orientation, nursing field, no prior experience in the medical or psychological field), and their clinical experience (e.g., years of practice, primary psychotherapy orientation, supervision, years of personal therapy). Responses to these preliminary questions will be used to automatically assign each participant to the appropriate study group. After the completion of the suicide risk assessment based on six vignettes describing hypothetical scenarios, all participants will be asked to indicate whether they have ever completed a suicide risk assessment training or previously used the C-SSRS scale.

#### Outcomes

2.4.2

The primary outcome will be the assessment of discrepancies in suicide risk estimates across study groups (between-subjects) and the evaluation of the stability of individual risk appraisal tendencies over time (within-subject), in order to identify specific patterns and factors that may influence variability and inter-rater agreement in risk estimation across different clinical scenarios.

The secondary outcome is the assessment of discrepancies in suicide risk estimates between the C-SSRS and No-C-SSRS conditions, in order to determine whether the use of a standardized suicide risk assessment instrument will lead to greater homogeneity in risk ratings across the study groups. To allow comparison of discrepancies between the two subgroups, suicide risk assessment will be expressed as categorical variables for participants assigned to the C-SSRS condition (low, moderate, high) and as ordinal scores for participants in the No-C-SSRS condition (from 1 to 9). Cut points were defined *a priori* to represent three clinically interpretable categories of risk intensity, corresponding to low (scores 1-3), intermediate (4–6), and high (7–9) perceived risk. This mirrors the three-level structure imposed by the C-SSRS while preserving the ordinal distribution of the original ratings (**Table 1**).

**Table 1 T1:** Conversion of the suicide risk estimates between the C-SSRS and No-C-SSRS conditions.

C-SSRS condition risk categories	No-C-SSRS condition risk scores
Low risk	1-2–3 scores
Moderate risk	4-5–6 scores
High risk	7-8–9 scores

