## Discussion

3

This study protocol outlines an innovative research project designed to examine both between-person and within-person variability in suicide risk estimates across several groups, including mental health professionals, other health professionals, medical and psychology students, and individuals from the general population. The study aims to produce evidence that can support enhancements in the training of healthcare professionals and the development of more consistent and reliable risk assessment strategies. Rather than attempting to improve statistical prediction of suicidal behavior, the CARE study focuses on the variability of human judgment in suicide-related situations, an issue that remains highly relevant even in clinical models that prioritize individualized formulation over categorical risk stratification. Furthermore, the study evaluates the effect of a brief, scalable training on a standardized instrument, the C-SSRS, reflecting real-world conditions in which such tools are frequently introduced without extensive training. Therefore, a transversal objective of this study is to determine whether the use of a standardized instrument, the C-SSRS, may reduce subjectivity in judgment and promote greater uniformity in suicide risk estimates across clinical and non-clinical participants. Indeed, understanding how non-professionals estimate suicide risk is important because individuals frequently encounter situations involving psychological distress in family, social, or workplace contexts, where interpretation of warning signs may influence help-seeking or referral behaviors. Additionally, by presenting different yet comparable vignettes at follow-up, the study examines whether individuals display stable risk attribution patterns across contexts, an approach that more closely reflects real-world clinical decision-making where identical cases are never reencountered.

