Overall, this project will represent one of the largest and most comprehensive initiatives aimed at comparing suicide risk assessment among mental health professionals, other healthcare professionals, and the general population. It will also provide insight into the effects of using standardized tools such as the C-SSRS on inter-rater and intra-rater variability, ultimately generating knowledge that can meaningfully contribute to strengthening suicide prevention efforts.

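### The secondary outcome and related statements credit the C-SSRS alone, but the randomised contrast is training plus C-SSRS against neither

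*Protocol article*

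**What the plan says.** **What is randomised.** Section 2.3.1 (Baseline assessment) states that "participants of each group (i–x) will be randomly assigned to one of the two conditions". There are two conditions and no third arm.

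**What the C-SSRS arm receives.** In the same section, "participants assigned to the C-SSRS condition will complete a brief training module on basic suicidology notions embedded within the online questionnaire before evaluating the vignettes". This module takes about five minutes and has two sections. The first defines six constructs, from thoughts of death to suicide death, "in order to reduce interpretative variability across respondents". The second explains how the C-SSRS works and how its answers map to risk categories. After that, "participants will be provided with access to the official Italian version of the C-SSRS".

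**What the other arm receives.** "The remaining participants will be asked to provide a subjective estimation of perceived suicide risk based on their impressions, knowledge, personal judgment, or clinical experience". No definitions, instructions or tool are described for this arm.

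**What the contrast is said to show.** The secondary outcome in Section 2.4.2 asks "whether the use of a standardized suicide risk assessment instrument will lead to greater homogeneity in risk ratings across the study groups". The Discussion gives as a transversal objective to "determine whether the use of a standardized instrument, the C-SSRS, may reduce subjectivity in judgment", and its last paragraph promises insight into "the effects of using standardized tools such as the C-SSRS on inter-rater and intra-rater variability". Aim 3 in Section 1.1 also names only the structured instrument, though in terms of association. HP 5, in that same section and tied to Aim 3, names brief training together with the C-SSRS. So do the Abstract and the Discussion paragraph on expected findings.

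**The concern.** The definitions are general suicidology content, not specific to the C-SSRS, and only one arm sees them. By the protocol's own account they are meant to make respondents interpret the material more uniformly. The secondary outcome asks whether ratings become more uniform. A shared vocabulary is therefore a competing explanation for any gain in agreement, written into the design.

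At stake is what the trial may conclude. The Discussion says that results may support wider use of standardised assessment in professional training. If the gain came wholly or partly from a short page of definitions, a report following the wording of Section 2.4.2 would present it as evidence for the instrument. No later analysis can correct this, because the data hold no comparison in which the definitions and the tool are separated.

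**Working it through.** The protocol gives no figure for this point, so the check compares the content of the arms with the claims.

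**1. Components by arm (Section 2.3.1)**

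| Component | C-SSRS | No-C-SSRS |
|---|---|---|
| Definitions of constructs (D) | yes | no |
| C-SSRS instructions (I) | yes | no |
| C-SSRS itself (T) | yes | no |

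**2. What the contrast identifies.** Let A(d, i, t) be the expected agreement when the components are present (1) or absent (0). The trial observes A(1,1,1) and A(0,0,0), so it estimates

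Δ = A(1,1,1) − A(0,0,0).

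Count the instructions as part of using the tool, which is the reading most favourable to the protocol. Then

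Δ = [A(1,0,0) − A(0,0,0)] + [A(1,1,1) − A(1,0,0)],

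that is, the effect of the definitions plus the effect of the instrument given the definitions. A(1,0,0) is never observed. The other possible instrument effect, A(0,1,1) − A(0,0,0), needs A(0,1,1), which is not observed either. This is one equation with two unknowns. The instrument's share cannot be bounded without further assumptions: if the parts worked against each other, it could even fall outside 0% to 100%.

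**3. Does anything else in the protocol separate the parts?**

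- *Follow-up (Section 2.3.2).* The module is not repeated, but the C-SSRS arm has already read it and controls never have. Exposure to the definitions stays tied to arm.
- *Prior suicide-specific training as a model term (Section 2.5.2).* This is a background characteristic that is not randomised. It does not split the randomised package.
- *Purpose of the module (Section 2.1).* The protocol presents the module as a means of understanding the tool. That can cover the C-SSRS instructions. It covers the general definitions less well, since they form a separate section with their own stated purpose.

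**4. Where the wording fits the design and where it does not**

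| Place | Exposure named | Fits? |
|---|---|---|
| Abstract (Background, Method) | training plus C-SSRS | yes |
| 1.1, HP 5 | training plus C-SSRS | yes |
| 2.1 Study design | training plus C-SSRS | yes |
| Discussion, expected findings | training plus C-SSRS | yes |
| 1.1, Aim 3 | instrument, associational | partly |
| 2.4.2, secondary outcome | instrument, causal | no |
| Discussion, transversal objective | instrument | no |
| Discussion, last paragraph | instrument | no |

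Four places need to be brought into line with the other four.

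**The case against.** The best defence is that the package is declared openly and often. The arms are called C-SSRS and No-C-SSRS, so naming the instrument may be shorthand for the condition, and Section 2.4.2 does define its comparison as one between conditions. The sentence just before the transversal objective speaks of a brief training on the instrument. Bundling is also a reasoned choice: Section 2.3.1 says that the module mirrors the orientation common in practice and that the study compares two assessment paradigms. The Introduction refers to the scale's own operational definitions, so some definitional content may belong to using it.

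Most of this stands. It rules out several stronger readings:

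- *A reader might infer that the protocol hides the training or contradicts itself throughout.* It does not; half of the places tabulated name the package.
- *A reader might infer that Aim 3 makes a causal claim for the instrument.* Its wording is associational. The causal form is in Section 2.4.2 and, less directly, in the Discussion.
- *A reader might infer that anything from none to all of the effect is due to the tool, and take that as a measured range.* It would only restate that the share is not identified.
- *A reader might infer that lay and student groups would gain most from the definitions.* The protocol does not say so, and its Discussion reports that most health professionals also lack suicide-specific knowledge.
- *A reader might infer that controls should be shown the definitions.* Section 2.5.1 defines the primary outcome for power on the 1 to 9 ratings of the No-C-SSRS arm, compared across ten groups. Training that arm would change the quantity being compared, and the instructions and response format would still differ between arms.

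What the defence does not reach is the wording of the outcome itself. Shorthand is acceptable in an arm label. It is not acceptable in the sentence that defines what the secondary comparison will determine, when a co-intervention aimed at nearly the same target is given to one arm only.

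**Conclusion.** The concern holds as a mismatch between the claim and the design. The trial can estimate the effect of brief training plus use of the C-SSRS against unstructured judgment without either. It cannot estimate the effect of the instrument alone, which is what the secondary outcome, the transversal objective and the closing statement name, and what Aim 3 names more weakly.

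The reach is limited. The primary between-group comparison is untouched, and randomisation still supports a comparison of the two conditions as packages. No numerical size can be given, because the instrument's share is not identified.

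The conclusion rests on two readings of Section 2.3.1: that controls see no definitions, as the description of their task implies, and that the definitions could affect agreement, which is their stated purpose. It does not rest on the difference in response format between the arms. That is a separate obstacle to interpretation and would remain after this point is settled.

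**What to change.** Restate Aim 3 (Section 1.1), the secondary outcome (Section 2.4.2), and the transversal objective and closing statement (Discussion) as the effect of *brief training plus use of the C-SSRS versus unstructured judgment without either*, in line with HP 5. Add one sentence saying that no conclusion about the instrument alone will be drawn from this contrast.

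Keep the definitions out of the No-C-SSRS arm, so that its ratings remain untrained for the primary ten-group comparison.

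The cost is wording only. Procedures, sample size and data collection do not change, and the edit can be made even if recruitment has begun. The price is a slightly narrower secondary claim: a gain in agreement would support the package and leave open which part produced it.
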